# The effectiveness of antioxidant vitamins C and E in reducing myocardial infarct size in patients subjected to percutaneous coronary angioplasty (PREVEC Trial): study protocol for a pilot randomized double-blind controlled trial

**DOI:** 10.1186/1745-6215-15-192

**Published:** 2014-05-29

**Keywords:** Percutaneous coronary angioplasty, Ischemia-reperfusion, Oxidative stress, Vitamin C, Vitamin E, Acute myocardial infarction

## Abstract

**Background:**

Acute myocardial infarction (AMI) is the leading cause of mortality worldwide. Oxidative stress has been involved in the ischemia-reperfusion injury in AMI. It has been suggested that reperfusion accounts for up to 50% of the final size of a myocardial infarct, a part of the damage likely to be prevented.Therefore, we propose that antioxidant reinforcement through vitamins C and E supplementation should protect against the ischemia-reperfusion damage, thus decreasing infarct size.

The PREVEC Trial (Prevention of reperfusion damage associated with percutaneous coronary angioplasty following acute myocardial infarction) seeks to evaluate whether antioxidant vitamins C and E reduce infarct size in patients subjected to percutaneous coronary angioplasty after AMI.

**Methods/Design:**

This is a randomized, 1:1, double-blind, placebo-controlled clinical trial.

The study takes place at two centers in Chile: University of Chile Clinical Hospital and San Borja Arriarán Clinical Hospital.

The subjects will be 134 adults with acute myocardial infarction with indication for percutaneous coronary angioplasty.

This intervention is being performed as a pilot study, involving high-dose vitamin C infusion plus oral administration of vitamin E (Vitamin-treatment group) or placebo (Control group) during the angioplasty procedure. Afterward, the Vitamin-treatment group receives oral doses of vitamins C and E, and the Control group receives placebo for 84 days after coronary angioplasty.

Primary outcome is infarct size, assessed by cardiac magnetic resonance (CMR), measured 6 and 84 days after coronary angioplasty.

Secondary outcomes are ejection fraction, measured 6 and 84 days after coronary angioplasty with CMR, and biomarkers for oxidative stress, antioxidant status, heart damage, and inflammation, which will be measured at baseline, at the onset of reperfusion, 6 to 8 hours after revascularization, and at hospital discharge.

**Discussion:**

The ischemia-reperfusion event occurring during angioplasty is known to increase myocardial infarct size. The cardioprotective benefits of high doses of vitamin C combined with vitamin E have not been fully explored. The PREVEC Trial seeks to determine the suitability of the therapeutic use of vitamins C and E against the reperfusion damage produced during angioplasty.

Patient recruitment opened in February 2013. The trial is scheduled to end in March 2016.

**Trial registration:**

ISRCTN56034553

## Background

Primary percutaneous coronary angioplasty (PCA) is recognized as the most useful way to recover coronary flow in the context of acute myocardial infarction (AMI). Myocardial salvage and limitation of infarct-size expansion are the principal mechanisms whereby patients with ST-segment-elevation myocardial infarction (STEMI) benefit from reperfusion [1]. Despite these important advances in pharmacologic treatment and reperfusion strategies, heart failure is a functional consequence of AMI that determines poor long-term prognosis in coronary patients [2]. Among others, global left ventricular function has always been viewed as an important prognostic factor after AMI. Different strategies have been assayed to preserve left ventricular function and reduce infarct size in patients undergoing primary PCA for STEMI [3,4], but no clinical benefits have been obtained.

Currently, it is widely accepted that cardiac magnetic resonance (CMR) imaging is the gold-standard method to measure infarct size associated with AMI in clinical practice [5-8] and in clinical trials [9]. CMR can also measure accurately and reproducibly ejection fraction, ventricular volumes and cardiac mass [5]. Infarct size has been deemed an “important trial end-point” in the Joint ESC/ACCF/AHA/WHF Task Force for the Redefinition of Myocardial Infarction [10] and is a well-known outcome in trials that evaluate amelioration of reperfusion injury, [11-15] because its variation reflects the interaction of multiple physiologic and metabolic factors while providing a direct measure of the amount of myocardial cell loss [16]. This direct measure is especially valuable in the context of AMI, in which functional measures, due to the phenomena of myocardial stunning or myocardial hibernation, may not reflect the long-term compromise of the heart.

Reperfusion injury presents as damage to the myocardium after blood restoration subsequent to a critical period of coronary occlusion [17]. Ischemia–reperfusion is a clinical problem associated with procedures such as thrombolysis, angioplasty, and coronary bypass surgery, which are commonly used to establish the blood reflow and minimize the damage of the heart due to severe myocardial ischemia. Reperfusion injury includes a series of events: (a) reperfusion arrhythmias, (b) no-reflow phenomenon “microvascular damage, (c) myocardial stunning “reversible mechanical dysfunction,” and (d) lethal reperfusion “cell death,” which may occur either together or separately [18,19].

Two main hypotheses, oxidative stress and Ca^2+^ overload, have been proposed to explain the pathogenesis of ischemia–reperfusion injury [20,21]. Concerning this, oxidative stress, which is usually associated with increased formation of reactive oxygen species (ROS), modifies phospholipids and proteins, leading to lipid peroxidation and oxidation of thiol groups; these changes alter membrane permeability and configuration and generate functional modification of various cellular proteins [22].

Several studies have proposed the essential role of ROS in the pathogenesis of myocardial ischemia–reperfusion injury. In ischemic-reperfused hearts, many alterations, such as depression in contractile function, arrhythmias, change in gene expression, and loss of adrenergic pathways, have been observed [23]. Similar changes have been reported in hearts perfused with various ROS-generating systems. Furthermore, pretreatment of cardiac subcellular organelles with ROS showed similar changes. Thus, alterations in the myocardium during ischemia–reperfusion were suggested to be in part due to oxidative stress. In addition, ischemia–reperfusion was found to increase H_2_O_2_, cytosolic free Ca^2+^ concentration, malondialdehyde (MDA) content, and the formation of conjugated dienes in the heart. Treatment of the heart in animal models with antioxidant enzymes, superoxide dismutase (SOD), plus catalase protected against these changes [24,25]. ROS seem to increase significantly after a few minutes of reperfusion, but the increase during ischemia alone is still controversial.

On the basis of these changes, it has been suggested that the increase of superoxide anion and other ROS during reperfusion leads to lipid peroxidation and sulfhydryl group oxidation. It has been demonstrated that endothelial cells, inflammatory cells (that is, neutrophils and macrophages), and cardiomyocytes are all capable of generating ROS through several enzymatic reactions. It has been proposed that a burst of ROS from endothelial cells and cardiomyocytes during early reperfusion can influence nearby neutrophils, setting up a local cycle of amplified cellular response through released inflammatory mediators.

Furthermore, neutrophils become sensitized (primed) to activating factors, such as chemotactic cytokines, after they adhere to the endothelium, and thus generate much greater quantities of ROS. After the initial burst of ROS at the onset of reperfusion, later events such as transendothelial migration of neutrophils and macrophages, might participate in delayed ROS generation during reperfusion [26,27]. Activated neutrophils produce superoxide as a cytotoxic agent as part of the respiratory burst via the action of membrane-bound NADPH oxidase on molecular oxygen. Neutrophils also produce the free radical nitric oxide (NO) that can react with superoxide to produce peroxynitrite, the most powerful oxidant agent of nitrogen-reactive species (NOS), which may decompose to form hydroxyl radical [28].

In AMI, a clinical model of oxidative stress, ROS are generated in the ischemic myocardium, especially after reperfusion. ROS directly injure the cell membrane and cause cell death [29]. However, ROS also stimulate signal transduction to elaborate inflammatory cytokines(for example, tumor necrosis factor-α (TNF-α), interleukin (IL)-1β, and IL-6), in the ischemic region and surrounding myocardium as a host reaction. Inflammatory cytokines also regulate cell survival and cell death in the chain reaction with ROS. Apoptosis or programmed cell death is a distinct form of destruction of the cell, which is associated with synthesis of enzymes that degrade and fragment its own DNA. Updated information suggests that ischemia followed by reperfusion significantly induces myocardial injury by an apoptotic death pathway.

To understand the potential signaling mechanisms involved in ROS-triggered apoptosis, recent reports showed that cytosolic Ca^2+^overload and enhanced activity of the mitogen-activated protein kinase (MAPK) family during reperfusion can participate in induction of ROS-mediated apoptosis, in addition to necrosis, and eventually could be a determinant in infarct size [30].

Cell death was once viewed as unregulated. It is now clear that at least a portion of cell death is a regulated cell-suicide process. This type of death can exhibit multiple morphologies. One of these, apoptosis, has long been recognized to be actively mediated, and many of its underlying mechanisms have been elucidated. Moreover, necrosis, the traditional example of unregulated cell death, is also regulated in some instances. Autophagy is usually a survival mechanism but can occur in association with increased ROS, leading to cell death. Little is known, however, about how autophagic cells die [31]. Apoptosis, necrosis, and autophagy occur in cardiac myocytes during myocardial infarction, ischemia-reperfusion, and heart failure. Pharmacologic or genetic inhibition of apoptosis and necrosis lessens infarct size and improves cardiac function in these disorders [32].

ROS and NOS are major initiators of myocardial damage during reperfusion. Accordingly, AMI is usually initiated by myocardial ischemia due to coronary artery obstruction. In the ischemic myocardium, ROS are generated by a prooxidant state especially enhanced after reperfusion. Thus, neutrophils are the primary source of ROS during reperfusion. Endothelial cells and cardiomyocytes can also generate ROS. Increased ROS production is mainly due to activation of xanthine oxidase (enzyme that catalyzes the formation of uric acid with the co-production of superoxide) in endothelial cells [33], mitochondrial electron-transport chain reactions in cardiomyocytes, and NADPH oxidase in inflammatory cells [34]. Under these conditions, the enzymatic antioxidant effect is relevant against the detrimental effects of ROS. In agreement with this view, it has been reported that the transgenic mice in which superoxide dismutase (SOD) is overexpressed, infarct size is markedly reduced [35,36]. Accordingly, allopurinol, a xanthine oxidase inhibitor, has been demonstrated to block the superoxide production in ischemia–reperfusion settings involving organs such as heart [37], liver [33], kidney [38], and small intestine [39].

Therefore, it should be expected that a reinforcement of the antioxidant defense system through ROS scavengers results in a cardioprotective effect during the myocardial reperfusion. After an ischemic episode of the myocardium, left ventricle remodeling is known to occur; although its underlying mechanism is multifactorial, ROS and inflammatory cytokines may cause a cardiodepressive reaction [40-42]. It is of interest that ROS also stimulate the production of inflammatory cytokines and, inversely, inflammatory cytokines stimulate ROS formation. In the chronic stage, ROS and inflammatory cytokines activate the matrix metalloproteinases [43,44], thereby eliciting degradation of collagens, which may cause a slippage in myofibrillar alignment, causing left ventricular dilation [45].

Major evidence exists on the contribution of ROS to myocardial damage in AMI in humans. Therefore, it should be expected that treatments with antioxidant agents or upregulation of endogenous antioxidant enzymes could protect against reperfusion injury. Some studies have suggested that antioxidant agents attenuate the left ventricular remodeling after AMI. In patients with AMI subjected to primary percutaneous transluminal coronary angioplasty, the pretreatment with the inhibitor of xanthine oxidase allopurinol resulted in effective inhibition of the generation of oxygen-derived radicals during reperfusion therapy and the recovery of left ventricular function [46]. More recently, the administration of edaravone, a free radical scavenger, in patients with AMI just before reperfusion, reduced significantly the infarct size and reperfusion arrhythmia [47]. However, other attempts, such as an intravenous bolus of either superoxide dismutase [48] or trimetazidine [49], showed no beneficial effects in the outcome of patients.

Most investigations on the health-protective effects of vitamins C and E have been focused merely on their antioxidant power. Nevertheless, the biologic properties of α-tocopherol and ascorbic acid have overwhelmed their antioxidant effects. Despite the enormous interest in antioxidant vitamins as potential protective agents against the development of human disease, the real contributions of such compounds to health maintenance and the mechanisms whereby they act remain unclear. Antioxidants, as well as numerous cardioprotective strategies for reducing lethal reperfusion injury, have been administered in patients with AMI [50]. Although the scientific rationale, epidemiologic data, and retrospective studies have been persuasive, prospective, randomized, placebo-controlled trials have so far failed to verify the actual benefit of antioxidant vitamins in human diseases [51-54]. Among the possible contributory factors likely to account for this discrepancy,the lack of consideration of basic aspects, such as the pharmacokinetic properties of antioxidant vitamins, will be discussed later. In agreement with this view, previous attempts to reduce free radical production after PCA for AMI by oral administration of vitamin C, failed to attenuate the increased production of F2-isoprostanes [55]. In turn, Jaxa-Chamiec *et al*. [56], performing a randomized, double-blind, placebo-controlled multicentric study in 800 patients, analyzed the effects of combined vitamins C and E, through infusion and capsules, could not demonstrate a major effect of this antioxidant treatment on the clinical outcome of patients, although diabetes patients showed a reduction in 30-day cardiac mortality [57]. It should be noted that the authors recognize as a limitation of the study the fact that the dose of vitamin C used in the study increases its plasma levels only up to 0.1 m*M*, a concentration 100 times lower than that required to scavenge superoxide anion.

Vitamin E, mainly α-tocopherol, is the major peroxyl radical scavenger in biologic lipid phases such as membranes or LDL [58,59]. The antioxidant action has been ascribed to its ability to act chemically as a lipid-based free radical chain-breaking molecule, thereby inhibiting lipid peroxidation through its own conversion into an oxidized product, α-tocopheroxyl. α-Tocopherol can be restored by reduction of the α-tocopheroxyl radical with redox-active reagents like vitamin C or ubiquinol [60]. In clinical studies of ischemia-reperfusion injury, positive effects of a multivitamin antioxidant solution, including vitamin E, were described for revascularization of the lower extremities, kidney transplantation, liver surgery, and aortic aneurysm repair [61-64]. Preoperative administration of vitamin E is safe, and it may have beneficial effects by reducing the impact of ischemia-reperfusion injury in liver surgery [65]. However, homologous studies in AMI are still lacking.

Regarding vitamin C, intraarterial administration of high doses of ascorbate has been demonstrated to abolish the *in vivo* effects of superoxide anion in the impairment of vascular endothelial function in subjects with essential hypertension [66]. In addition, recent *in vitro* studies have also been successful to study the effects of oxidative stress with and without this vitamin C concentration, thus validating the use of this concentration of ascorbate to counteract the effects of oxidative stress [66]. Vitamin C concentration in plasma is tightly controlled, and excess of vitamin C is excreted as a function of dose, being completely saturated at doses of 400 mg daily and higher, producing a steady-state plasma concentration of approximately 80 μ*M*[67]. Unfortunately, this concentration is not enough to scavenge superoxide anion. Therefore, in settings accompanied by oxidative stress, such as the myocardial ischemia-reperfusion cycle, a beneficial effect of oral administration of vitamin C in the prevention of oxidative damage should not be expected; however, intravenous infusion could be considered with this purpose. Indeed, superoxide reacts with NO at a rate 10^5^-fold greater than the rate at which superoxide reacts with ascorbic acid [68]. As a consequence, 10 m*M* ascorbate is needed to support its competition with NO for superoxide. In patients undergoing elective PCA, impaired microcirculatory reperfusion is improved by vitamin C infusion, suggesting that oxidative stress is implicated in such a phenomenon [69]. Also, in patients subjected to thrombolysis after AMI, superoxide dismutase in the blood was found to be significantly reduced, whereas the activity of the oxidant enzyme, xanthine oxidase, and MDA levels were found to be significantly increased. However, oral supplementation of vitamin C to the postreperfusion patients restored these parameters back to normal or near-normal levels [70]. Although higher ascorbate doses would be needed to reach a better protective effect, its biologic properties, other than that of scavenging ROS, may have some beneficial effect. The major source of ROS is their enzymatic production via NADPH oxidase, an enzyme subjected to downregulation by vitamin C. In addition, vitamin C prevents the oxidation of tetrahydrobiopterin, a cofactor of NO synthase that is highly sensitive to oxidation. When tetrahydrobiopterin is oxidized, endothelial nitric oxide synthase (eNOS) activity becomes uncoupled, resulting in the production of superoxide instead of NO, thus enhancing the oxidative damage [71].

Ascorbic acid and α-tocopherol act as potent hydrophilic and lipophilic antioxidants, respectively [72]. They also act synergistically; in aqueous compartments, ascorbic acid can recycle α-tocopherol in membranes by reducing the α-tocopheroxyl radical back to α-tocopherol [73]. Consequently, in vitamin-E-supplemented rat hearts, α-tocopherol diminishes rapidly without the addition of vitamin C during reperfusion [74].

Finally, it is noteworthy that vitamin C could also abrogate the beneficial effects of ischemic preconditioning in animal models, a phenomenon induced by a series of brief sublethal episodes of ischemia and reperfusion before a potentially lethal episode of ischemia that renders the heart more resistant to myocardial infarction [75].

### Pilot study objectives

It is hypothesized that patients subjected to percutaneous coronary angioplasty to restore the coronary blood flow previously impaired by an acute myocardial infarction, while receiving a short-term infusion of high doses of vitamin C, plus oral doses of the recommended dose of vitamin E, will have a smaller infarct size, as well as an attenuation of the functional and biochemical damage occurring during the reperfusion afterthe sudden loss of blood supply, as compared with placebo-treated patients.

The objectives of this study are to determine in patients subjected to PCA after AMI:

i. the efficacy of vitamins C and E in reducing myocardial infarct size;

ii. the protective effects of vitamin C and E in cardiac function, assessed by measurement of ejection fraction;

iii. the levels of lipid peroxidation and protein carbonylation at baseline and immediately after successful reperfusion, 6 to 8 hours after vascular recanalization and at discharge;

iv. the levels of antioxidant potential at baseline and immediately after successful reperfusion, 6 to 8 hours after vascular recanalization, and at discharge; and

v. the correlation between oxidative stress-related biomarkers and both the infarct size and ejection fraction at 6 and 84 days after vascular recanalization.

## Methods/Design

### Design

This double-blind, placebo-controlled, multicenter clinical trial will randomize in a 1:1 ratio to either placebo-treatment or vitamin-treatment groups. The study design is summarized in Figure 1.

**Figure 1 F1:**
[figure not shown]
CONSORT flowchart for PREVEC Trial.

### Study population

Patients of either sex, older than18 years, with an indication for primary percutaneous coronary angioplasty and experiencing their first acute myocardial infarction, admitted to University of Chile Clinical Hospital or San Borja Arriarán Clinical Hospital, will be invited to participate in the study. Inclusion and exclusion criteria are expressed in Tables 1 and 2, respectively.

**Table 1 T1:** Inclusion criteria of the study protocol

**Inclusion criteria**	
1	Subjects may be of either sex and must be at least 18 years old
2	Subjects must have indication of primary percutaneous coronary angioplasty (PCA):
	-Angina or equivalent at least 120 minutes in duration
	- Electrocardiogram with ST-segment elevation myocardial infarction that concerns more than two contiguous leads (>2 mm)
3	Presentation within 12 hours of symptoms onset
4	First myocardial infarction
5	Primary PCA must show a pre-PCA TIMI flow of 0
6	Subject must be able and willing to sign informed consent

**Table 2 T2:** Exclusion criteria of the study protocol

**Exclusion criteria**	
1	History of renal or hepatic insufficiency
2	History of renal lithiasis
3	History of heart failure (New York Heart Association III, IV)
4	Cardiogenic shock
5	Postprimary PCA TIMI grade flow of 0, 1, or 2
6	Any serious medical comorbidity that determines life expectancy <6 months
7	Current participation in any other clinical investigation
8	Pregnancy
9	Glucose 6-phosphate dehydrogenase deficiency

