### Sample size

Taking into account that until 50% infarct size is due to reperfusion damage, a minimal efficacy of the intervention is considered to reach a relative improvement up to 25% infarct size. Similar studies applying the same method have provided the accuracy of measurements as variance value. The sample size was calculated from the following formula [76]:

$$n=2{\left(\mathrm{ZS}+\mathrm{ZP}\right)}^{2}x\;S^{2}/{\left(\mathrm{MA}–\mathrm{MB}\right)}^{2}$$

Where *n* is the sample size for each group, “ZS” corresponds to the level of significance (5%), “ZP” represents the potency (80%), “MA” is the mean of supplemented group,MB, the mean of the placebo group (control), and S is the variance of CMR determination for assessment for IS. A 10% patient loss was considered for the purposes of this calculation. This calculation rendered a sample size of 66 patients for each branch (placebo and supplemented). This sample size is suitable to be covered by the population of patients being treated for PCA in the Cardiovascular Department, University of Chile Clinical Hospital, and Cardiovascular Center, San Borja Arriarán Clinical Hospital, during the estimated period (3 years).

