### Randomization and followup

Patients will be randomly allocated to one of the two groups. The allocation sequence will be centrally generated, stored, and assigned by using online randomization software (http://www.randomization.com) in random permuted blocks, each consisting of a box containing six treatment kits allocated in a placebo-to-vitamin treatment, 1:1 ratio for each participating center.

Random allocation is generated by intervention of the technician responsible for the treatment assignment to recruited patients, according to the sequence already established through the randomization method indicated previously. The reasons for losses and exclusions after randomization will be provided.

Neither participants, nor care providers, nor the investigators are aware of the treatment assignments. Adverse events, unintended effects and technical problems will be recorded.

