### Interventions

All patients will be asked to sign the informed consent before beginning the protocol. For those patients allocated to receive vitamin treatment, the intervention will be started as soon as the patient has signed the informed consent. The protocol will be started by administering an unique oral dose of vitamin E as α-tocopherol (800 IU) and an intravenous infusion of vitamin C as sodium ascorbate (320 m*M*) infused at a 10-ml/min flow rate during the initial hour and at 3 ml/min rate during the following 2 hours. Percutaneous coronary angioplasty will be performed about 30 minutes after initiating the vitamin C infusion. Oral doses of vitamin E (400 IU/day) and vitamin C (500 mg/12 hours) will be taken by the patients for 84 days after PCA.

For those patients allocated to receive placebo treatment, the 800-IU oral dose of vitamin E will be replaced for two vegetable oil capsules (400 mg each). The intravenous infusion of vitamin C will be replaced by an equal sodium chloride solution volume having the same osmolality as the vitamin C infusion administered to supplemented patients. The 400-IU oral doses of vitamin E will be replaced by vegetable oil (400 mg), and oral doses of vitamin C will be replaced with inert starch microgranules (500 mg). The pharmaceutical forms of vitamin C and E are indistinguishable from their respective placebos.

After the initial evaluation, patients will go to the catheterization laboratory. According to the standard protocol in AMI, an angiography will be performed to identify the infarct-related artery. The location and extent of AMI (number of arteries involved), percentage of stenosis, TIMI flow, type of stent, and so on, will be recorded. Immediately before coronary arteriography to confirm total occlusion of one coronary artery, a basal blood sample will be drawn from the antecubital vein. Three more blood samples will be obtained: immediately after successful reperfusion, at 6 to 8 hours after finishing the revascularization process and before hospital discharge.

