### Primary and secondary outcomes

Primary outcome will be infarct size, which will be measured with CMR at 6 and 84 days (12 weeks) after PCA. Both determination and data obtained by these procedures will be evaluated by two blinded independent individuals with the purpose of applying the concordance kappa index.

As our primary outcome is fully dependent on a high-quality blood-flow restoration to the ischemic myocardium region, we established as our criteria for successful reperfusion only patients who have a starting TIMI flow of 0 in the PCA and finish the procedure with TIMI flow 3, according to the most rigorous literature standards [77-79]. Secondary outcomes will be myocardial-damage biomarkers, oxidative stress- and inflammation-related biomarkers, and ejection fraction.

1. Ejection fraction: will be measured with cardiac magnetic resonance (CMR) at 6 and 84 days (12 weeks) after PCA. Both determination and data obtained by these procedures will be evaluated by two blinded independent individuals with the purpose of applying the concordance kappa index.

2. Oxidative stress-related biomarkers:

Plasma protein carbonylation

Antioxidant capacity of plasma: Ferric reducing ability of plasma (FRAP)

Plasma concentration of vitamins C and E

Thiol index: GSH/GSSG ratio in erythrocytes

Lipid peroxidation: F2-isoprostane and malondialdehyde levels in plasma and erythrocytes, respectively, will be measured.

3. Inflammation biomarkers:

High-sensitivity C-reactive protein

Leukocyte count by standard method

4. Myocardial-damage biomarkers:

Troponin, CK, and CK-MB will be measured in plasma with standard methods

Oxidative stress- and inflammation-related biomarkers and myocardial-damage biomarkers will be assessed through antecubital venous blood extraction, at the moment of enrollment (30 to 60 minutes before PCA), immediately after successful reperfusion, at 6 to 8 hours after finishing the revascularization process and before discharge, as previously described. The samples will be collected in chilled vacutainers containing disodium EDTA (final concentration, 4 m*M*) and centrifuged at 3,000 *g* for 10 minutes to separate the plasma from figurate elements. Erythrocytes will be subjected to hypotonic hemolysis by dilution with distilled water. Plasma and red blood cell lysates will be stored at -80°C until performing the biochemical analyses.

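### Excluding patients on post-PCA TIMI flow, after allocation and the start of the infusion, leaves the infarct-size comparison open to selection bias

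*Protocol article*

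**What the plan says.** The order of events is in the Interventions section. Allocated treatment begins once consent is signed, before the patient goes to the catheterization laboratory, and "Percutaneous coronary angioplasty will be performed about 30 minutes after initiating the vitamin C infusion".

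Two eligibility criteria can be checked only after that. Table 1, item 5 states "Primary PCA must show a pre-PCA TIMI flow of 0". Table 2, item 5 excludes "Postprimary PCA TIMI grade flow of 0, 1, or 2".

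The Primary and secondary outcomes section repeats the restriction. It says the primary outcome depends fully on good restoration of flow, and counts as successfully reperfused "only patients who have a starting TIMI flow of 0 in the PCA and finish the procedure with TIMI flow 3".

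The Randomization and followup section expects such removals: "The reasons for losses and exclusions after randomization will be provided". The Sample size section gives 66 patients per arm and adds "A 10% patient loss was considered for the purposes of this calculation". The article describes no analysis of all randomised patients.

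**The concern.** Post-PCA flow cannot act as an entry criterion for someone already allocated and infused. In practice it removes patients after treatment has begun. That is harmless only if treatment does not influence the variable, or if the variable is unrelated to the outcome. The protocol gives reason to doubt both conditions:

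- **Treatment may affect flow.** The Background lists no-reflow among the forms of reperfusion injury, which is what the vitamins are meant to prevent. It also reports that "impaired microcirculatory reperfusion is improved by vitamin C infusion", a result from elective PCA.
- **Flow is tied to the outcome.** The outcomes section makes infarct size depend on the quality of reperfusion.

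If the infusion helps flow, some patients with large infarcts reach TIMI 3 and stay in the vitamin arm, while their counterparts on placebo are removed. The TIMI 3 finishers in the two arms are then different kinds of patient. At stake is the validity of the primary comparison, and with it the claim in the Discussion that any reduction in infarct size can be attributed only to less reperfusion damage.

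**Working it through.** **1. The planned effect.** The article gives the formula n = 2(Z_α + Z_β)²S²/(MA − MB)², 5% significance, 80% power, a 25% relative reduction, 10% loss and 66 per arm. It gives no means, no SD and no sidedness, so 66 can only be solved backwards.

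- Evaluable per arm: 66 × 0.9 = 59.4.
- Two-sided (assumed): (1.960 + 0.842)² = 7.849, so the effect is √(2 × 7.849/59.4) = 0.514 SD. Reading the loss as 66/1.1 = 60 gives 0.511 SD. I use 0.51.
- One-sided, the same step gives 0.456 SD.

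**2. Size of the selection bias.** No rate of TIMI failure is given, so every rate here is an assumption. Let p_P and p_V be the proportions ending below TIMI 3 on placebo and on vitamins, with p_V < p_P. Suppose the patients whose flow the treatment rescues have infarcts h SD larger than the other TIMI 3 finishers, and no patient's flow is made worse. The vitamin mean then moves upwards by

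shift = (p_P − p_V) × h / (1 − p_V).

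| p_P | p_V | h (SD) | Shift (SD) | Share of 0.51 SD |
|---|---|---|---|---|
| 10% | 5% | 0.5 | 0.026 | 5% |
| 10% | 5% | 1.0 | 0.053 | 10% |
| 15% | 8% | 1.0 | 0.07/0.92 = 0.076 | 15% |
| 15% | 5% | 1.0 | 0.105 | 20% |
| 20% | 10% | 1.5 | 0.167 | 33% |

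All these shifts run against vitamins. If treatment worsened flow, the sign reverses: 5% on placebo, 10% on vitamins and h = 1 give 0.053 SD in favour of vitamins.

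The type I error also moves. With 15% against 5%, h = 1 and 10% other loss, 50.5 and 56.4 patients remain and the standard error is √(1/50.5 + 1/56.4) = 0.194 SD. If infarct size itself is unaffected, the shift of 0.105 SD raises the two-sided error from 5% to about 8.5%.

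**3. Power, as a condition.** Suppose 66 counts randomised patients, post-PCA exclusions are not replaced, and they come on top of 10% other loss. Evaluable per arm = 59.4 × (1 − excluded).

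| Post-PCA exclusions | Evaluable per arm | Power, normal formula, 0.514 SD | Power, t test, 0.511 SD | Randomised per arm to keep 80% (66/(1 − excluded)) |
|---|---|---|---|---|
| 5% | 56.4 | 78.0% | 76.8% | 70 |
| 10% | 53.5 | 75.7% | 74.5% | 74 |
| 15% | 50.5 | 73.3% | 72.0% | 78 |

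If the 10% must absorb these exclusions as well, 5% excluded leaves 1 − 0.9/0.95 = 5.3% for every other loss, and 10% leaves none. The Discussion names claustrophobia, loss between days 6 and 84, and lost samples as expected losses. It does not name TIMI exclusions.

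**The case against.** The other side has several fair arguments.

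- **No passage says that vitamins change TIMI grade.** The vitamin C evidence concerns the microcirculation in elective PCA, and the no-reflow passage mentions neither vitamins nor TIMI grade. This stands: the bias is possible, not shown. A reader might infer that the primary comparison is demonstrably biased, and the article does not support that.
- **Exclusions are made blind.** True, and if the infusion does not affect flow they balance in expectation. But blinding does not help when the variable used for exclusion itself responds to treatment.
- **In the expected scenario the bias is conservative.** It is, if treatment improves flow. The opposite direction cannot be ruled out, and a bias towards no effect also costs the trial its ability to detect benefit.
- **TIMI 0-to-3 is a deliberate, referenced choice in a mechanistic pilot, and analysis sets are often left to the analysis plan.** The mechanistic question is legitimate and can be answered in a subset. The restriction, however, is fixed here as an eligibility rule. If excluded patients are not scanned, no later plan can recover their infarct size, and the regression under consideration cannot adjust for unmeasured outcomes.
- **The 10% may already cover these losses.** A reader might infer that it does not. The article does not say what the 10% covers or whether 66 counts randomised or evaluable patients, so that inference is not established. Nor can power of 50–67% be charged to this criterion. That range needs an assumed 20–40% of patients without pre-PCA TIMI 0, a separate criterion that the fix below retains.

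**Conclusion.** The point holds for the post-PCA criterion. Allocation and dosing precede it, the protocol's rationale makes it open to treatment effect, and the protocol links it to infarct size. Restricting the primary comparison to TIMI 3 finishers therefore gives up the protection of randomisation.

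The direction and size of the bias are unknown. Under the illustrative rates it is about 0.08 SD against vitamins, 15% of the planned effect. Across differences of 5 to 10 percentage points between arms and infarcts 0.5 to 1.5 SD larger, it ranges from 5% to 33%. These figures rest on assumed failure rates and on a back-solved two-sided effect of 0.51 SD.

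The power point is conditional. If 66 counts randomised patients and none are replaced, power falls below 80% once all losses together exceed 10%. It is about 72–78% with 5–15% post-PCA exclusions on top of 10% other loss, depending on the formula.

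Pre-PCA TIMI 0 is also read after the infusion starts, but it is less exposed. The Discussion reasons that ascorbate cannot pass a fully occluded artery.

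**What to change.** 1. Remove post-PCA TIMI flow below 3 as a ground for exclusion from the primary analysis population.
2. Define that population as all randomised patients with blindly read pre-PCA TIMI 0, analysed in their assigned arm whatever the final flow.
3. Perform the day 6 and day 84 CMR in all of them.
4. Report the TIMI 0-to-3 subset as a sensitivity analysis, and add a sensitivity analysis of all randomised patients, because pre-PCA flow is also learned after dosing starts.
5. Report post-PCA TIMI flow by arm.
6. State whether 66 per arm counts randomised or evaluable patients and what the 10% covers. The total needs settling at the same time: 2 × 66 = 132, while the Abstract gives 134.

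The cost is an amendment, some additional CMR scans of a kind the trial already performs, and slight dilution of the effect if low-flow patients cannot benefit. The Trial status section reports 43 patients enrolled, so most of the planned sample could still be recruited under the amended rule. For those already excluded, it should be stated whether CMR was done.
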